## Abstract

**Background:**

To date, there has been no systematic research on the intermediate level service (level 2) in outpatient palliative care that was introduced in Germany in 2017. Accordingly, the Polite research project aims at: (1) investigating the current state of level 2 palliative care and (2) developing recommendations for its optimisation.

**Methods:**

The multi-perspective, observational study will follow a mixed-methods approach across two study phases. In phase 1a, quantitative routinely collected data from a statutory general local health insurance provider will be used to identify patients who received level 2 or other outpatient palliative care in the years 2017–2019. In phase 1b, a questionnaire will be sent to all registered general practitioners (GPs) in Lower Saxony to collect information on the number and characteristics of physicians offering level 2 palliative care. In phase 1c, a quantitative, standardised online questionnaire for teams providing specialised outpatient palliative care will be administered to assess the interfaces of level 2 palliative care. In phase 2a, the results from phases 1a–c will be discussed in an expert workshop with the aim of developing ideas to adapt and optimise level 2 outpatient palliative care. Finally, in phase 2b, the empirically derived recommendations from phases 1 and 2a will be agreed upon via a multi-round Delphi survey involving experts with sufficient influence to promote the project results and recommendations nationally.

**Discussion:**

The results of the project will facilitate the optimisation of outpatient palliative care, as well as its administration, nationwide.

**Trial registration:**

The study was registered in the German Clinical Trials Register (Deutsches Register Klinischer Studien) (Registration N° DRKS00024785); date of registration: 06^th^ May 2021) and is searchable under the International Clinical Trials Registry Platform Search Portal of the World Health Organization, under the German Clinical Trials Register number.

## Introduction

### Background

According to sociodemographic trends, it is estimated that at least 23.3% of German residents will be over 67 years old in 2030 [1]. The absolute number of German residents over the age of 80 years is expected to increase from 4.4 million in 2013 to more than 9 million in 2060 [1]; this projected figure corresponds to approximately 12–13% of future population estimates. Rising morbidity and health care costs among German’s elderly population are also expected [2].

Current estimates of need suggest that 40.7–96.1% of dying people could benefit from palliative care. An analysis of all deaths in 2013 in Germany found an estimated need of 78% across all age groups [2]. In general, approximately 80–90% of people requiring palliative care can be adequately cared for through generalist outpatient palliative care (level 1) [2]. The European Association for Palliative Care (EAPC) white paper on standards and norms for hospice and palliative care in Europe states: ‘Whereas a palliative care approach will provide adequate care for many of these patients, it has been estimated that at least 20% of cancer patients and 5% of non-cancer patients require specialist palliative care in the last year of their life’ [3]. Although palliative care offerings in Germany have recently expanded and the number of service providers has increased, there is still a great need for palliative care, especially in rural areas [4].

In Germany, outpatient and inpatient palliative care has undergone very dynamic development to respond to sociodemographic changes and palliative care needs. Important milestones in the political effort to improve palliative care in Germany have included the introduction of specialist outpatient palliative care (level 3) in the Social Code Book V (SGB V) in 2007 [5]; the inclusion of palliative care within the statutory health insurance system of general patient care in the Hospice and Palliative Care Act of December 2015 [6]; and the expansion of the Uniform Value Scale (‘Einheitlicher Bewertungsmaßstab’, EBM) to include generalist outpatient palliative care (level 1) by general practitioners (GPs) in 2013 [4, 7]. In 2016, during the implementation of the Hospice and Palliative Care Act, an agreement was reached for the establishment of an intermediate level of generalist outpatient palliative care (level 2) [8, 9].

The new legislation aimed at introducing level 2 generalist outpatient palliative care as an intermediate step between basic level 1 care and level 3 specialist outpatient palliative care in the pyramid-like care structure [5, 8]. In a white paper on standards and norms, for example, the EAPC described and recommended the graduation of: 1) a palliative care approach, 2) general palliative care and 3) specialist palliative care [3]. This three-level system of outpatient palliative care was already a feature of several international health care systems.

The proposed expansion was based on the assumption that some seriously ill and dying people were under-served by level 1 palliative care, but not good candidates for level 3, due to a lack of complex symptoms, among other reasons. Thus, level 2 palliative care was proposed to treat patients with an incurable, progressive and advanced disease for which curative therapy was no longer possible or desired, but who still required interdisciplinary and comprehensive palliative medical treatment, appropriate for their stage of disease [10, 11]. Level 2 care could be administered in outpatient settings, such as patients’ private homes, as well as assisted living facilities, inpatient nursing homes, day hospices and inpatient hospices. However, while level 1 palliative care can be provided and billed by all GPs, only GPs with special qualification could offer palliative care at levels 2 or 3.

The overarching goals of level 2 outpatient palliative care were: a) to improve the care of seriously ill patients (in all age groups) with palliative care needs/wishes in their last phase of life, b) to improve the provision of outpatient palliative care, c) to allow patients to die in the environment of their choice and d) to establish needs-based structures, coordination and on-call care [10, 11]. These goals were considered sufficient to address the essential problem areas of end-of-life care for people in Germany.

### Study aims

To date, there have been no systematic evaluations of level 2 palliative care since it was first implemented in Germany in 2017. Scientific research is needed to: 1) uncover the barriers to and facilitators of level 2 palliative care, 2) provide empirical data on the administration of this new form of outpatient palliative care and its impact on other forms and 3) develop recommendations to improve the acceptance and feasibility of level 2 palliative care. Therefore, the Polite study aims at investigating how (and to what extent) level 2 palliative care is integrated into end-of-life care in Germany, and delineating its general impact on patient care.

Specifically, the study aims at answering the following questions:

Which level 2 palliative care components are applied in practice, and how?What are the experiences of care providers and policy makers with respect to level 2 palliative care? What do they identify as the barriers to and facilitators of level 2 palliative care, in practice?What adaptations to level 2 palliative care are reasonable and necessary to support its administration and optimise end-of-life care?

### Aims of the study protocol

The present protocol describes a mixed-methods study involving qualitative and quantitative methods and participatory aspects. The research aims at making an original contribution to the palliative care literature by increasing the transparency of the administration of outpatient palliative care in Germany. Publication of the study protocol represents the first step in this process. The authors believe that the project partners, scientists studying similar topics, and the broader scientific community will be interested in consulting the study protocol to obtain an overview of the project. Furthermore, health care insurance providers and policy makers will find the study design for systematic research on outpatient palliative care highly relevant.

### Study design

The multi-perspective, observational study will follow a mixed-methods approach, spread across two research phases (Fig 1).

**Fig 1 pone.0256467.g001:**
[figure not shown]
Mixed-methods study design. AOKN = statutory health insurance provider in Lower Saxony; GPs = general practitioners; PC = palliative care; WP = work package.

### Setting

Study phase 1 will be conducted in Lower Saxony. Lower Saxony is the second largest federal state in Germany, comprised of both urban and rural areas. As its characteristics are similar to those of other federal states, the results of the research will be generalisable throughout Germany. Importantly, Lower Saxony includes urban areas with continuous GPs and palliative care providers, as well as rural areas with low population density and challenging health care structures.

### Study phases and data collection

In phase 1, work package 1a, quantitative routinely collected data from the statutory health insurance provider Allgemeine Ortskrankenkassen Lower Saxony (AOKN) will be used to analyse the development of level 2 outpatient palliative care services over time and to identify patients who died in 2019 and received outpatient palliative care services (at any level). Sociodemographic and disease-related data for these patients will be collected and compared according to those who received level 2 palliative care versus those who received palliative care at levels 1 or 3. The consortium will reveal the care trajectories of these patients, the patients who received different forms of outpatient palliative care and the transitions that occurred between levels of outpatient palliative care. In addition, the use of health care services beyond palliative care (but alongside level 2 palliative care) will be examined from billing records; such services might include medical specialists or hospital admissions. These data are expected to reveal the extent to which level 2 palliative care is implemented. Finally, a comparison with data from patients deceased in 2017 will show on a macro level whether (and to what extent) the introduction of level 2 palliative care shifted the type and administration of palliative care at levels 1 or 3. The data required for this will be extracted and analysed by the AOKN.

In phase 1, work package 1b, a quantitative, standardised questionnaire for GPs will be developed on the basis of the literature, previous scientific findings, available political statements and contributions from relevant professional associations. The online survey will be sent to all (N = 5,158) GPs registered in Lower Saxony to collect information on the number and characteristics of physicians offering level 2 palliative care. A response rate of approximately 15% (n = 774) is expected.

In phase 1, work package 1c, comparable to work package 1b, a quantitative, standardised online questionnaire for teams providing specialist outpatient palliative care (level 3) will be developed. The questionnaire will aim at quantifying respondents’ experiences with working at the interface of level 2 and level 3 palliative care. It will also seek to ascertain how work at the interfaces between palliative care levels 1, 2 and 3 does or does not succeed in practice, and which practical implementation models for level 2 have been developed. The questionnaire will be sent to all (N = 59) registered specialist outpatient palliative care teams in Lower Saxony, and a response rate of approximately 50% (n = 30) is expected.

In phase 2, work package 2a, the results from phases 1a–c will be presented and discussed in an expert workshop at Hannover Medical School. The discussion will aim at developing ideas to adapt and optimise level 2 outpatient palliative care. Approximately n = 20 care providers and stakeholders from hospice and palliative care in Germany will participate in the expert workshop. A drop-out rate of 10% due to illness, other commitments and personal reasons is expected. Personal invitations will be sent out until the target number of N = 22 experts is reached. The result of the work package 2a will be initial formulations of possible recommendations, which will be subjected to further scrutiny in work package 2b.

In phase 2, work package 2b, the empirically derived recommendations from phases 1 and 2a will be agreed upon via a multi-round Delphi survey [12] involving n = 40 experts with sufficient influence to promote the project results and recommendations nationally, including participants from phase 2a. To compensate for an expected participation rate of 20–30% and a drop-out rate of 10%, approximately N = 120 experts will be invited. Delphi survey data will be collected with the aid of an online tool. Participants will be asked to indicate their level of agreement with each individual recommendation on a 4-point Likert scale, with regards to relevance, clarity and feasibility. Free text fields will also be included for participants to provide additional comments on the recommendations.

The project team is presently developing the research infrastructure with respect to (e.g.) data protection, ethical approval, contracts with project partners and public relations to prepare for the project start. Moreover, strategies to support the development of address registers for GPs and specialist outpatient palliative care teams are being discussed.

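### The comparison of 2019 with 2017 decedents can describe a change in level 1 and level 3 use, but cannot assign that change to the introduction of level 2

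*Protocol article*

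**What the plan says.** The Protocol article, Study phases and data collection, ends its account of work package 1a with a comparison between two years of death. It states that "a comparison with data from patients deceased in 2017 will show on a macro level whether (and to what extent") a shift took place. The shift in question, in the protocol's terms, is that "the introduction of level 2 palliative care shifted the type and administration of palliative care at levels 1 or 3". The extraction and the analysis are left to the insurer: "The data required for this will be extracted and analysed by the AOKN". The Data analysis section makes the work package 1a analysis quantitative and descriptive.

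Three other places bear on how that comparison can be read:

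- **Background**, on the setting in which level 2 arrived: "In Germany, outpatient and inpatient palliative care has undergone very dynamic development to respond to sociodemographic changes and palliative care needs". The same section adds that "palliative care offerings in Germany have recently expanded and the number of service providers has increased".
- **Study aims**, on timing: "there have been no systematic evaluations of level 2 palliative care since it was first implemented in Germany in 2017".
- **Abstract, Methods**, on the data window: the insurer's data serve to "identify patients who received level 2 or other outpatient palliative care in the years 2017–2019".

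No comparison region, comparison insurer or series for levels 1 and 3 before 2017 is named.

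**The concern.** The sentence names a cause (the introduction of level 2), an effect (a shift at levels 1 or 3) and a size (how far). The contrast behind it is two annual groups of decedents from one insurer in one federal state. Whatever else altered the use of levels 1 and 3 between 2017 and 2019 enters the same difference.

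The error could run either way. If level 3 was growing for other reasons, that growth could conceal patients moving from level 3 to level 2. Conversely, a change unrelated to level 2 could be read as its consequence.

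The result is put to use. Findings of phase 1 go to the expert workshop, from there to a Delphi survey of experts chosen for their national influence, and under Dissemination and implementation the recommendations may inform changes in the law. Whether level 2 draws patients from level 3, adds to it or leaves it alone is a question on which a wrong sign could mislead.

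**Working it through.** Work package 1a states no effect size, utilisation rate or growth rate, so there is no figure of the plan's own to reproduce. The check has three steps: what the contrast estimates, how far background change could matter, and whether the baseline is clean.

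**1. What the contrast estimates**

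For one level of care, let *p* be the share of decedents using it, *b* the background change in that share from 2017 to 2019 (in percentage points), and *e* the effect of level 2 over the same period.

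Observed change = *p*(2019) − *p*(2017) = *b* + *e*

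This is one equation in two unknowns. Estimating *b* needs either a group in the same years with little or no level 2, or a trend from before level 2. The article names neither. The data window starts in 2017. The requirement of continuous insurance in the calendar year before death reaches back to 2016 for the 2017 decedents, but as an eligibility condition and not as a trend series.

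**2. How far background change could matter (assumed figures)**

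Assume a 2017 share of 10% or 25%, and background growth *g* of 3%, 5% or 10% a year over two years.

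*b* = share × ((1 + *g*)² − 1)

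| 2017 share | *g* per year | Change with no level 2 effect (*e* = 0) | Change if *e* = −2 points |
|---|---|---|---|
| 10% | 3% | 10 × 0.0609 = +0.61 | −1.39 |
| 10% | 5% | 10 × 0.1025 = +1.03 | −0.97 |
| 10% | 10% | 10 × 0.21 = +2.10 | +0.10 |
| 25% | 3% | 25 × 0.0609 = +1.52 | −0.48 |
| 25% | 5% | 25 × 0.1025 = +2.56 | +0.56 |
| 25% | 10% | 25 × 0.21 = +5.25 | +3.25 |

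The third column shows growth mimicking an effect; the fourth shows it shrinking, cancelling or reversing one. Put additively: with *e* = −2 and *b* anywhere from 0 to +4, the observed change runs from 0 − 2 = −2 to 4 − 2 = +2. These figures show that confounding is possible. They do not show that it is this large in Lower Saxony.

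**3. Whether the baseline is clean**

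Study aims dates the first implementation of level 2 to 2017, which is the comparison year. If a fraction *s* of the eventual effect *e* was already present among 2017 decedents, the contrast returns *b* + (1 − *s*)*e*. The documents do not give *s*. An earlier baseline year would remove *s* but leave *b*.

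**What a contrast between districts would return**

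Difference in change, high- minus low-uptake districts = (*b*_high − *b*_low) + (*e*_high − *e*_low)

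This isolates the effect only if the first bracket is zero (parallel trends), *e*_low is zero (an unexposed comparator) and 2017 is free of level 2. If the comparator has some uptake, or the baseline is partly exposed, the second bracket is diluted.

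**The case against.** The strongest defence is that the study is descriptive and this comparison is one element among several. Work package 1a also plans care trajectories, transitions between levels, a comparison of level 2 recipients with recipients of levels 1 or 3, and the development of level 2 over time; work package 1c surveys level 3 teams about the interfaces. The sentence leaves open that no shift will be found, and it speaks only of the macro level. Level 2 was introduced nationwide, so an unexposed group may not exist. Regional stratification is the kind of detail that an article leaves to the full plan.

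Much of this stands. The other elements do inform movement between levels, so it would be wrong to say that the study as a whole would report no displacement. Nor is the absence of a stratified table a fault in a condensed article. What does not stand is the defence by description: the analysis is descriptive, but the conclusion promised from it is causal and quantified, and both the contrast and its reading are fixed in the text. The reference to the macro level states the aggregation and does not qualify the attribution.

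Stronger readings are tempting but not supported:

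- **That the protocol says care was expanding regardless of level 2.** Background gives no date or rate for the expansion and does not call it independent of level 2. The Hospice and Palliative Care Act of December 2015 is not a clean rival cause either, since level 2 was agreed while that Act was being implemented.
- **That the comparison covers the whole state.** It covers one insurer's members, aged 18 or older at death and continuously insured in the year of death and the calendar year before.
- **That districts without level 2 exist as a ready control.** The Setting section mentions "rural areas with low population density and challenging health care structures", which concerns care structures and not level 2 uptake. Background says that only specially qualified GPs could offer levels 2 or 3, which makes uneven uptake plausible but does not establish it.

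**Conclusion.** The concern holds in a limited form. The 2017-to-2019 comparison returns the sum of any level 2 effect and any background change, and nothing in the article allows the two to be separated. The protocol itself describes a field in motion, so background change is a realistic rival explanation, though that it arose independently of level 2 is an inference. Because 2017 is the introduction year, the baseline may also contain some level 2 care.

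The size cannot be taken from the documents. Under the assumed inputs, background growth alone gives between +0.61 and +5.25 points, and a true −2 points appears as anything from −1.39 to +3.25. A reader might infer that the comparison is uninformative, or that a district contrast would recover the true effect. Neither follows. As a description of change the comparison is sound, and a district contrast recovers the effect only under the conditions shown in the working, which are not assured here.

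**What to change.** **Wording (needed).** State that the comparison of 2019 with 2017 decedents will describe the change in level 1 and level 3 use between the two years, and drop the attribution to the introduction of level 2. Note that 2017 is the first year of level 2. Carry the same wording into the material for the workshop and the Delphi survey. This costs nothing and needs no further data.

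**Added table (if feasible).** If the insurer's data hold district of residence and level 2 uptake varies, tabulate the change in level 1 and level 3 use by district uptake (none or low versus high). Report the difference in change between the groups as associated with level 2 uptake, not as caused by it. This is one further descriptive table from data that the insurer already analyses.

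**Downside of the table.** Uptake may follow local level 3 supply, because both levels depend on specially qualified physicians, so parallel trends are not assured. Low-uptake comparators and the 2017 baseline would tend to dilute the contrast. Small districts may have to be pooled.

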### Inclusion, exclusion and termination criteria

In phase 1, work package 1a, only secondary data will be analysed; thus, there will be no participant recruitment. Inclusion criteria will depend on the type of analysis (e.g. utilisation of level 2 outpatient palliative care or death). For deceased patients, the inclusion criteria will comprise: an age of 18 years or older at the time of death and continuous insurance during the year of death and the preceding calendar year.

In phase 1, work packages 1b and 1c, online surveys will be conducted with all registered GPs and all level 3 specialist outpatient palliative care teams in Lower Saxony. The aim will be to achieve a full assessment of both groups in this federal state. Therefore, no further inclusion or exclusion criteria will be needed. Each survey participant will independently decide whether to participate, as well as when to cease participation, if desired. No termination criteria will be defined.

In phase 2, work packages 2a and 2b, experts will participate in a workshop and/or Delphi survey. Participants will be selected according to the principle of diversity, in order to ensure the adequate representation of inpatient, ambulatory, generalist and specialist service providers and all interfaces with level 2 palliative care. The exclusion criteria will be comprised of insufficient German language skill and less than 1 year of experience in hospice and palliative care. Experts will be able to terminate their participation at any time.

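### The 2017 deaths are not a clean pre-introduction group, so comparing them with 2019 deaths describes change from the introduction year and does not measure the effect of introducing level 2

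*Protocol article*

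**What the plan says.** Under Study phases and data collection, work package 1a profiles insured persons who died in 2019. It closes with a reference comparison: "a comparison with data from patients deceased in 2017 will show on a macro level whether (and to what extent") the introduction of level 2 moved care at levels 1 or 3. The Data analysis section makes all of work package 1a descriptive.

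On timing, the Abstract (Background) speaks of an "intermediate level service (level 2) in outpatient palliative care that was introduced in Germany in 2017", and Study aims says "there have been no systematic evaluations of level 2 palliative care since it was first implemented in Germany in 2017". The only 2016 event is an agreement: "In 2016, during the implementation of the Hospice and Palliative Care Act, an agreement was reached for the establishment of an intermediate level" (Introduction, Background). The Abstract (Methods) plans to "identify patients who received level 2 or other outpatient palliative care in the years 2017–2019", so the plan itself expects level 2 recipients in 2017. The article gives no month of introduction.

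**The concern.** To show what an introduction changed, one needs a reference group that lived and died without the new service. By the article's own dates, 2017 does not supply one: some, most or all of the 2017 deaths may have occurred when level 2 was already available. The text states no split of 2017, no earlier reference year and no concurrent comparison group.

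A second difficulty is separate. The Introduction says that "outpatient and inpatient palliative care has undergone very dynamic development" and lists the inclusion of level 1 in the fee scale in 2013 and the Hospice and Palliative Care Act of December 2015. A change between two single years contains whatever those developments were still producing.

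Study aims names the impact of level 2 on other forms of care as a research need. The phase 1 results feed the expert workshop and the Delphi recommendations, which the Dissemination section says may inform legislation. A finding of no shift could mean that level 2 displaced nothing, or that the reference year was already exposed. A finding of a shift could be trend.

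**Working it through.** The article gives no effect size, rate or sample size for this comparison, so there is no figure to reproduce. The check is of dates, followed by an illustration of size.

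**Dates.** Agreement: 2016. Introduction and first implementation: 2017. Years in which level 2 recipients are sought: 2017–2019. Reference deaths: 2017. Index deaths: 2019. The reference year is therefore the introduction year.

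**What the contrast contains.** For any measure of level 1 or level 3 use, let
- B = its value in 2017 had level 2 not existed,
- D = the full shift due to level 2 at its 2019 uptake,
- T = the change from 2017 to 2019 that would have occurred without level 2,
- f = the share of 2017 deaths on or after the start of level 2,
- r = uptake among those deaths relative to 2019.

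If the shift is proportional to uptake, the 2017 value is B + f·r·D and the 2019 value is B + D + T. The difference is

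D·(1 − f·r) + T.

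This is one observed number for D, f·r and T together.

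**Size of the contamination term.** The start month m is not in the document, so a range is shown. With deaths assumed uniform over the year, f = (13 − m)/12. The share of D that stays visible is 1 − f·r. For a July start, f = (13 − 7)/12 = 0.5; with r = 0.5 the visible share is 1 − 0.5 × 0.5 = 75%.

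| Start month (assumed) | f | r = 0.1 | r = 0.25 | r = 0.5 | r = 1 |
|---|---|---|---|---|---|
| January | 100% | 90% | 75% | 50% | 0% |
| April | 75% | 92.5% | 81% | 62.5% | 25% |
| July | 50% | 95% | 87.5% | 75% | 50% |
| October | 25% | 97.5% | 94% | 87.5% | 75% |
| December | 8% | 99% | 98% | 96% | 92% |

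Contamination ranges from negligible to total, and nothing in the article narrows it.

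**With a clean reference.** If all reference deaths precede the start, f = 0 and the difference becomes D + T, with T now running from the new reference period to 2019. The contamination is gone, but T is not. A cleaner reference year alone would still not attribute the change to level 2.

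**The case against.** The best defence is that the article never calls 2017 a baseline without level 2. The contrast can be read as introduction year against a more established phase, within work declared descriptive. If level 2 started late in 2017 or spread slowly, most of a real shift would remain visible: even a January start with uptake at one tenth of the 2019 level leaves 90%. The 2017 decedents also carry 2016 history, because eligibility requires "continuous insurance during the year of death and the preceding calendar year". And none of the three specific study questions asks for an effect estimate.

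Part of this stands. A reader might infer that the comparison cannot reveal any shift. That is too strong, since the loss may be small. But the sentence at issue promises more than description: it undertakes to show whether the introduction caused a shift, and how large. The 2016 history does not rescue that. The text does not confine the comparison to it, and care in the year before the year of death is not at the same distance from death as care in the last months.

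Three further readings are tempting and are not supported:
- *Unequal look-back between the cohorts, because the Abstract names 2017–2019.* The eligibility rule sets the same two calendar years for both cohorts: 2016–2017 and 2018–2019.
- *Shares distorted by a denominator restricted to palliative care recipients.* No such denominator is stated for this comparison. Study population and the eligibility criteria for deceased patients contain no receipt requirement.
- *That this is the only analysis bearing on other levels of care.* Work package 1a also examines transitions between levels, and work package 1c surveys level 3 teams about the interfaces. Neither supplies a reference period without level 2, but both bear on the question.

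**Conclusion.** The point holds in limited form. By the article's own dates the reference year is the introduction year, so the claim to show whether and to what extent introducing level 2 shifted levels 1 or 3 is not supported as written. The contamination acts towards no change. Its size is unknown: in the illustration, between 0% and 99% of the true shift remains visible. Those figures rest on three assumptions: deaths uniform over 2017, a shift proportional to uptake, and start months and uptakes chosen only to span the possibilities. The trend term is a separate limit; it can act in either direction and does not depend on these assumptions. What the comparison can support is a description of how level 1 and level 3 use differed between the introduction year and 2019.

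**What to change.** State the date on which level 2 became billable, and split the 2017 decedents at that date. The 2016 data this needs are already implied by the insurance criterion. If the start was at or near the beginning of 2017, the split leaves few or no unexposed deaths, and the alternative applies: take 2016 decedents as the reference, provided the insurer can supply 2015–2016 data. The article does not say whether it can.

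Preferably, show level 1, 2 and 3 use by year or quarter of death through 2019, so that any movement already under way is visible alongside the change.

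In any case, replace the promise to show the effect of the introduction with a statement that the analysis will describe the change in level 1 and level 3 use between 2017, identified as the introduction year, and 2019. The years named should be adjusted if another reference is adopted.

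The rewording costs nothing but a more modest conclusion. The split costs a few more tables. The 2016 reference may need one more year of extracted data, so it is best settled before the extraction is specified.
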